### Risk assessment and monitoring

Common side effects in tDCS experiments are mild headache, itching, fatigue [69]. All experimenters using these techniques will undergo thorough training about how to deal with and minimize these risks. Clinical members of the research team will assess seriousness, causality (relatedness), an expectedness of any adverse event experienced by the participant with reference to the most recent regulatory tDCS guidelines [57]. Data on reported side effects will be reviewed following each treatment session by clinicians treating and supporting the participant during treatment. Following completion of intervention, course reported side effects will be reviewed by the PI and clinical co-PI. If none of the participants recruited to the study can tolerate the data collection or intervention, the trial will be stopped.

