#### Randomization and blinding

A computer programme will generate forty random flags identifying the patient’s group (20 flags equal to 1 for ACTIVE, 20 flags equal to 0 for SHAM). Flag order will then be shuffled and a participant’s unique ID (sub-01, sub-02, … sub-40) associated to a flag, following the order of attendance. The study design is double blind: participants and the assessors will not know until the end of the intervention if the participant had received active or sham brain stimulation. A member of the research team (not the assessor) will program two stimulation protocols (active and sham) on the stimulation device, which will be set to operate into blind mode. As such, the person who administers the stimulation will be blind to the details of the protocol. Meaning they will not be able to see the details of the protocol. Patients are then randomly assigned to one or the other protocol, resulting in an intervention blind both to the assessor and the patient.

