#### Brain stimulation protocol

Brain stimulation will be administered using a Starstim 8 brain stimulation device (Neuroelectrics®). Standardized locations derived from electroencephalography will be used to place the electrodes over the right dorsolateral prefrontal cortex (DLPFC). We will use a bipolar setup, includes two circular Ag/AgCl electrodes (area = 3.14 cm^2^) filled with conductive gel and placed on F4 (anode) and Fp1 (cathode). Reference electrodes will be attached to the earlobe and impedances will be measured throughout the stimulation and kept below 20 kΩ. We will use a total current intensity of 2 mA for 20 min, preceded by 30 s ramping up and followed by 30 s ramping down (total stimulation time = 21 s). With these parameters and Ag/AgCl electrodes (area of 3.14 cm^2^) we obtain a current density of approximately 0.6 mA/cm^2, slightly higher than the one obtained with larger electrodes, but still well below the threshold for risk of tissue damage [57–59]. The simulated current distribution obtained with such setup is shown in Fig. 1. During sham stimulation, we will use the same setup as in the active condition but after ramping up, the current will be brought back to zero and the ramp up/down process repeated 30 s before the end of the 21 min time interval (total sham stimulation time = 21 min). We have recently completed data collection with the same protocol in 28 elderly and another study on stroke patients is undergoing: in these participants, brain stimulation has been well received.

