##### Outcome assessment (T1)

On the following day participants perform a series of pre-training outcome tasks (T1; Table 4), administered by an assessor, to measure their baseline working memory capacity and to assess, during and at the end of the training intervention, the efficacy of the training and the stimulation regime. These tests will not be used to determine eligibility. The assessor is blind to group assignment (control vs active).

On the same day as T1 testing, the assessor will familiarize them with the stimulation procedure (which is identical for sham or active) and the training game. The member of the team administering the training answers any questions about the study. Overall, this second session lasts for about 1 h.

##### Training phase 1

On the 10 consecutive training days after the T1 session, depending on the group, participants will receive active or sham brain stimulation (see section 3.5.2). As the assessor, who administer brain stimulation, is blind to the intervention, the procedure will be the same for both groups. At the same time, both groups complete the working memory training exercise for 20 min. If the WM training finishes before the stimulation, participants are asked to wait until the end of the tDCS session (20 min). Before each training session, participants are also asked to answer short questions (level of alertness, engagement, etc.). Once the training session and the stimulation are complete, the participant fills in a feedback form on the side effects of brain stimulation experienced, if any.

Participants will complete 10 consecutive training sessions (2 weeks, excluding weekends. Each session should take about 45 min (~ 10 min setting up of tDCS and ~ 20 min of WM training). This phase will be completed at home, with the assistance of the trainer. An attempt will be made to start the intervention on a Monday, therefore aiming to have breaks in the stimulation at the same point in the 2 weeks, and to keep the training time consistent over days. Nevertheless, administration time and date will be recorded. By the end of these 10 sessions, participants will be familiar with the training game and will be able to confidently undertake the training by themselves in the next 15 sessions.

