## Discussion

The overarching aim of the study is to assess if a specific form of non-invasive brain stimulation, namely direct current, has an impact on performance during a working memory training regimen in patients with an acquired brain injury. The novelty of our research resides in the combination of brain stimulation with working memory training: while the two interventions have been used before in clinical populations, to the best of our knowledge this is the first trial looking at the combination of both in acquired brain injury patients.

The focus of this study are chronic brain injury patients. These patients are no longer in a clinical setting but have returned home and are seen by the Community Brain Injury Service for community-based rehabilitation. These aspects make the proposed intervention particularly suitable for the population under study, as individuals can undertake the long (5 weeks) training regimen in the comfort of their home, at their own pace, minimizing the risk of drop-outs otherwise likely with long interventions. Our intervention is suitable for home healthcare, and, if proven successful, could represent a valuable asset to the NHS to address brain injury related cognitive impairment without putting excessive burden on patients and carers, and the NHS. At the same time, this trial will provide valuable knowledge to health authorities and the research community on the potential of non-invasive brain stimulation and training regimens in addressing chronic cognitive impairment in clinical populations. If successful, our study will provide evidence that a restorative approach to cognitive rehabilitation is possible, and an alternative to compensatory approaches currently used.

By evaluating performance at 1 month after the completion of the training regimen, we will shed new light on the long-term effects of cognitive training, also identifying potential modulatory effects of brain stimulation. This finding will, in turn, inform future protocols, in order to maximise improvement of cognitive functions while minimizing the amount of training necessary. Ultimately, patients would want these interventions to have an impact on their everyday life: we therefore also ask patients to self-evaluate (with the PRECIS questionnaire) how the training regimen impacted their cognitive functions and, indirectly, on their ability to cope with everyday situations.

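### The only trial-level stop stated in the article is all-or-none across both arms, so one tolerating participant, active or sham, disables it

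*Protocol article*

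**What the plan says.** The section Risk assessment and monitoring of the protocol article closes with the trial-level stop: "If none of the participants recruited to the study can tolerate the data collection or intervention, the trial will be stopped". No other condition for stopping the whole trial appears in the article.

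The same section sets out the surrounding safety process. On adverse events: "Clinical members of the research team will assess seriousness, causality (relatedness), an expectedness of any adverse event experienced by the participant". On side effects: "Data on reported side effects will be reviewed following each treatment session by clinicians treating and supporting the participant during treatment". At the end: "Following completion of intervention, course reported side effects will be reviewed by the PI and clinical co-PI". None of these steps is linked to a decision to pause or stop the trial.

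Three other places bear on how the condition behaves:

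- Randomization and blinding fixes the arms at "20 flags equal to 1 for ACTIVE, 20 flags equal to 0 for SHAM", so half of those recruited are sham participants.
- Brain stimulation protocol describes sham as a ramp up, a return to zero and a repeat of the ramp near the end, against 2 mA for 20 minutes on active. It also reports earlier use of the same protocol, where "in these participants, brain stimulation has been well received".
- The Discussion says that, to the authors' knowledge, "this is the first trial looking at the combination of both in acquired brain injury patients".

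**The concern.** A stopping condition is useful only if it can be met in the situations that would call for a stop. This one requires that nobody tolerates the study. Suppose many active participants give up because of the stimulation while sham participants carry on without trouble. That is the pattern which should prompt a pause, and the stated condition would not be met.

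The stake is participant safety and orderly conduct. If staff look to this sentence for guidance, a run of active-arm discontinuations does not meet it, and a pause would rest on judgement outside the stated rule. No estimate, test or sample size depends on it.

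**Working it through.** **Logic.** Let T be the number of recruited participants who have tolerated the study. The condition is T = 0. T counts people over both arms and does not fall, so once T = 1 the condition is false for the rest of the trial. The phrase about data collection or intervention can be split into two conditions (nobody tolerates the one, or nobody tolerates the other), but each part still lapses with one tolerating participant. A sham participant can tolerate the intervention as assigned, although this says little about tolerance of 2 mA for 20 minutes. Hence 20 of 20 active participants intolerant and 1 sham participant tolerant gives T = 1, and no stop. This conclusion needs no rate.

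**Inputs for an illustration.** The article gives N = 40, allocated 20 active and 20 sham in shuffled order. It gives no intolerance rate, so all rates below are assumptions. Write pa for intolerance on active and ps for intolerance on sham. The article states no figure for this rule, so there is nothing of its own to reproduce.

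**Formula.** Among the first k participants the number on active, A, is hypergeometric (k drawn from 20 and 20). The probability that the condition can no longer be met, once the outcomes of those k are known, is

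1 − Σ P(A = a) · pa^a · ps^(k−a), summed over a from 0 to k.

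Example, pa = 1 and ps = 0.05, k = 1: 1 − (0.5 × 1 + 0.5 × 0.05) = 0.475.

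| pa / ps (assumed) | k = 1 | k = 2 | k = 4 | k = 8 |
|---|---|---|---|---|
| 5% / 5% | 0.950 | | | |
| 10% / 10% | 0.900 | 0.990 | | |
| 50% / 5% | 0.725 | 0.926 | 0.995 | |
| 100% / 5% | 0.475 | | 0.934 | 0.997 |

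For the condition to hold over all 40 in the last row, every participant must fail: 1^20 × 0.05^20, about 1 × 10^−26.

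**A reachable trigger for comparison.** Take a pause at c or more discontinuations for intolerance among the first 20, pooled over arms. The arm split is again hypergeometric. Given the split, the count is the sum of two binomials, Bin(A, pa) and Bin(20 − A, ps).

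| pa / ps (assumed) | P(pause), c = 4 | P(pause), c = 5 |
|---|---|---|
| 5% / 5% | 0.016 | 0.003 |
| 10% / 10% | 0.133 | 0.043 |
| 30% / 5% | 0.476 | 0.261 |
| 50% / 5% | 0.860 | 0.696 |

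A pooled count cannot tell a mild active-arm excess from uniform intolerance: with c = 4, 15% / 5% gives 0.132, practically the same as 10% / 10%.

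**The case against.** The strongest reply is that the sentence is asked to do a job it was not given. It says the trial stops if nobody can tolerate it; it does not say that the trial stops only then. The mention of data collection suggests a feasibility backstop. A reader might infer that the trial has no working protection against harm, or that a related serious adverse event could not halt it. The documents do not support that. Side effects are reviewed by clinicians after each session, adverse events are assessed for seriousness, causality and expectedness, and stimulation is given in person by staff trained in tDCS and basic life support. The exclusions cover epilepsy, a family history of it, seizure since the injury and skull defects. An ad hoc halt stays possible. A condensed article may also leave serious adverse event rules to the full protocol, so their absence here is not the point.

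A reader might also infer that the condition is spent almost at once. That goes too far. Tolerating the study involves 10 stimulated sessions, 3 more weeks of training and a 1-month follow-up, and no evaluation time is stated. Several people could be enrolled before the first is known to have tolerated it. The k in the working counts participants with known outcomes, not calendar time.

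Nor should the novelty statement carry much weight. The same sentence of the Discussion notes that both interventions have been used before in clinical populations, and the same stimulation protocol had been completed in 28 elderly people.

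What stands is narrower. Even as a tolerability backstop, the condition responds only to complete failure in both arms. It is the only trial-level stop shown, and it sits in the section on risk. Rules held elsewhere would not make this sentence workable.

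**Conclusion.** The point holds in limited form. The stated condition can be met only while nobody in either arm has tolerated the study, so it has practically no sensitivity to partial intolerance or to intolerance confined to the active arm. This follows from the wording and the 20/20 allocation alone. The probabilities show how little chance the rule has under assumed rates; they are not estimates for this trial, and the thresholds of 4 and 5 in 20 are illustrations.

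The finding concerns a rule that is stated and badly fixed. It does not show that participants are unprotected, and it does not touch the primary comparison. Severity is minor to moderate: the gap is partly covered by the review already described, but the repair is cheap.

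**What to change.** Replace the sentence with a trigger that can be reached. Pause recruitment and stimulation for review by the PI and clinical co-PI when the number of discontinuations for intolerance reaches a value set in advance by the clinical members, for example 4 of the first 20. Count over both arms together, so that no one has to be unblinded. Let the same sentence start that review on any serious adverse event judged related to stimulation, unless the full protocol already does so.

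The cost is a one-sentence amendment and a running tally. The side-effect form is filled in after a completed session, so one line is needed to record sessions stopped for intolerance.

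The downside is an occasional unnecessary pause: about 2% at 5% intolerance in both arms and 13% at 10% for 4 of 20, or 0.3% and 4% for 5 of 20. The stricter threshold detects less: 70% against 86% when intolerance is 50% on active and 5% on sham. A count by arm would be more specific, but it needs a designated unblinded holder of the assignments, which the article does not set up.

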### Dissemination policy

Results of this study may be submitted for publication in a peer reviewed journal. On completion of the study, the data will be analysed and tabulated, and a final study report prepared and made available on ClinicalTrials.org, the study has been registered on the database. Results will be published in peer-reviewed journals and presented at relevant scientific meetings. Participants will be asked whether they would like to receive a copy of the final report, or a simplified version of it, and will be provided with this if they wish. Dissemination will be achieved through conference presentations, public talks and community talks. Upon publication, the anonymised dataset may be made available to other researchers upon request.

## Discussion

The overarching aim of the study is to assess if a specific form of non-invasive brain stimulation, namely direct current, has an impact on performance during a working memory training regimen in patients with an acquired brain injury. The novelty of our research resides in the combination of brain stimulation with working memory training: while the two interventions have been used before in clinical populations, to the best of our knowledge this is the first trial looking at the combination of both in acquired brain injury patients.

The focus of this study are chronic brain injury patients. These patients are no longer in a clinical setting but have returned home and are seen by the Community Brain Injury Service for community-based rehabilitation. These aspects make the proposed intervention particularly suitable for the population under study, as individuals can undertake the long (5 weeks) training regimen in the comfort of their home, at their own pace, minimizing the risk of drop-outs otherwise likely with long interventions. Our intervention is suitable for home healthcare, and, if proven successful, could represent a valuable asset to the NHS to address brain injury related cognitive impairment without putting excessive burden on patients and carers, and the NHS. At the same time, this trial will provide valuable knowledge to health authorities and the research community on the potential of non-invasive brain stimulation and training regimens in addressing chronic cognitive impairment in clinical populations. If successful, our study will provide evidence that a restorative approach to cognitive rehabilitation is possible, and an alternative to compensatory approaches currently used.

By evaluating performance at 1 month after the completion of the training regimen, we will shed new light on the long-term effects of cognitive training, also identifying potential modulatory effects of brain stimulation. This finding will, in turn, inform future protocols, in order to maximise improvement of cognitive functions while minimizing the amount of training necessary. Ultimately, patients would want these interventions to have an impact on their everyday life: we therefore also ask patients to self-evaluate (with the PRECIS questionnaire) how the training regimen impacted their cognitive functions and, indirectly, on their ability to cope with everyday situations.

Finally, our intervention falls within the remit of home healthcare medicine, with the potential to be fully self-administered by the patient (with support of carer if required) in their home. We will therefore collect data on the usability of the training, to inform future development in line with homecare technologies.

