**Method:**

Patients with a working memory deficit will be recruited and assigned to two age-matched groups receiving working memory training for 2 weeks: an active group, receiving tDCS (2 mA for 20 min), and a control group, receiving sham stimulation. After the end of the first 2 weeks, both groups will continue the working memory training for three more weeks. Outcome measures will be recorded at timepoints throughout the intervention, including baseline, after the 2 weeks of stimulation, at the end of the working memory training regimen and 1 month after the completion of the training.

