## Aims and objectives

The aim of this research project is to investigate the impact of combined working memory training and tDCS protocols in individuals following a brain injury in terms of the training gains, change in objective measures of working memory, mood and fatigue, as well as participants’ perceptions of day-to-day memory function and subjective benefit of the training program.

Specifically, our primary objective is to determine if the combination of tDCS and working memory training is superior to working memory training alone to improve working memory function in an n-back task in an ABI population. The key secondary objectives are to determine if the combination of brain stimulation with working memory training can:
boost performance in other cognitive domains (attention, executive functions)speed training gainslengthen improvement duration to 1 monthincrease improvement magnitude

To address the above questions, we will use a randomized clinical trial, assessor- and patient-blinded with two parallel groups and a simple randomization with a 1:1 allocation ratio.

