### Recruitment

Forty adults between the age of 18 and 69 years will be recruited through the Community Brain Injury Service. Patients will be randomly assigned to one of two experimental groups: an active (or right-sided tDCS) group and a control (or SHAM) group. All patients will receive WM training. As there is evidence that age modulates individual responses to both tDCS [50–52] and training regimens [53, 54], the two groups will be age-matched in two age subgroups: those aged between 18 and 45 years and those aged between 46 and 69 years, randomised within age range. Other factors may also influence the impact of the intervention on patients, including medications, time since injury, baseline performance, and these factors will be included as regressors in the analysis whenever appropriate. To reduce the variability due to different locations of lesions, patients with lesions underneath the electrodes (that could modify the induced electric field) will be excluded. Finally, as explained in the following, patients will only be included if they present with a working memory deficit, but no general intellectual impairment.

As the aim of this research is to improve working memory, only participants with a working memory impairment will be included. As we are focusing on improving a documented working memory deficit, we will not attempt to distinguish between pathologies (unless otherwise determined by the exclusion criteria for tDCS, e.g. a lesion underneath the electrodes), rather we will screen patients based on working memory performance. Final analysis will explore differences between pathologies. To identify a working memory impairment, cognitive tests from the Wechsler Adult Intelligence Test (WAIS-IV) and the Wechsler Memory Scale (WMS-IV) will be administered. These tests are administered to every patient as part of the routine care protocol. We will use the following scores:

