### Intervention

The BRAINSTORMING trial is designed as a randomized clinical trial, assessor and patient blinded with two parallel groups, and a simple randomization with a 1:1 allocation ratio. Participants identified as having reduced working memory will be randomly assigned to one of two experimental groups: an active (or right-sided tDCS) group and a control (or SHAM) group. Individuals included in the active group will receive 20 min of tDCS to the right dorsolateral prefrontal cortex while completing the WM training, whereas participants in the control group will complete the WM training while receiving sham (e.g., placebo) stimulation. Participant blindness to group membership will be achieved by the use of a SHAM protocol, which simulates current stimulation.

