#### Outcome measures

Our primary outcome measure will be the training gain*,* obtained by looking at the relative change in n-level (# items maintained in working memory) over the course of the training, as well as performance increments in the pre−/post-test outcome measures in the stimulation relative to the control (SHAM) group. Transfer of improvement to other cognitive domains will be assessed by comparing performance in a battery of cognitive tasks given at different times points throughout and after the intervention. Maintenance of improvement will be assessed by comparing outcome measures (Table 4) at different occasions during and after the conclusion of the study.
Training gain. Performance in training is measured as the N level reached on every session. The training gain is defined as the difference in N levels at two time points. Accuracies and reaction times at trial level will also be collected. In addition, we will administer a non-adaptive visuo-spatial task (N = 1, *N* = 2, *N* = 3), to allow us to quantify improvements at different testing points in terms of accuracy and reaction times in the trained cognitive domain.Transfer. We will use spatial tasks that test the same cognitive process as the training task to evaluate transfer to closely related tasks. We will use the same spatial addition and the symbol span task also used in the screening phase. We also will use the Dalhousie Computerized Attention Battery (DalCAB) [68], 8 cognitive tests to assess attentional functions in the vigilance, orienting and executive control attention network. Tasks are described in Table 4. Reaction time and accuracy will be computed for each task.Maintenance. To identify how long benefits of training and or stimulation are maintained in time, we will compare changes between outcome measures at T3 and at T4, 1 month after the end of the intervention.Everyday life improvement. It is important to understand whether improvement in cognitive tasks targeting specific processes can transfer to improvement in everyday life activities. We will use a self-reported questionnaire (PRECIS, Patchick et al., Clinical Rehabilitation, [66]) to evaluate if and how training in cognitive tasks targeting specific processes impacts on everyday activities.

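### Both arms receive the same training, so the everyday-life definition and the long-term-effects claim credit to training what the trial can show only for added tDCS

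*Protocol article*

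**What the plan says.** **Design.** The protocol article describes "two parallel groups and a simple randomization with a 1:1 allocation ratio" (Aims and objectives). Under Recruitment it states "All patients will receive WM training", and under Intervention that "participants in the control group will complete the WM training while receiving sham (e.g., placebo) stimulation". After the two stimulation weeks, "both groups will continue the working memory training for three more weeks" (abstract, Method). That is 10 plus 15 sessions in each arm. No untrained, waiting-list or control-training arm is described.

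**Objectives.** The primary objective is to "determine if the combination of tDCS and working memory training is superior to working memory training alone". The key secondary objectives ask whether adding stimulation improves other domains, speeds gains, extends them to 1 month or enlarges them.

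**Statements about training itself.**
- Outcome measures, Everyday life improvement: PRECiS is used "to evaluate if and how training in cognitive tasks targeting specific processes impacts on everyday activities".
- Outcome measures, Maintenance: T3 is compared with T4 to see how long benefits of training, of stimulation, or of both persist. That item names no comparison between arms.
- Discussion: "we will shed new light on the long-term effects of cognitive training, also identifying potential modulatory effects of brain stimulation".
- Discussion: "If successful, our study will provide evidence that a restorative approach to cognitive rehabilitation is possible", which the same sentence goes on to present as an alternative to the compensatory approaches now in use.

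**The concern.** The randomised comparison isolates stimulation. Whatever training does is common to both arms and cancels in the difference. A statement about what training does to daily life, or how long its effect lasts, therefore has to rest on change over time without a control. The section on data collection, management, analysis, and monitoring plans mixed and repeated-measures ANOVAs and follows up any significant main effect. A main effect of time would be such a change. Read together with the Everyday-life definition and the Discussion, it could be reported as a training benefit even if training had none. The Discussion addresses the NHS and health authorities, so the distinction matters to those readers.

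**Working it through.** **The article's own figure.** The only power figure is N of about 48 at effect size 0.73, alpha .05, power 0.80, for active versus sham. It reproduces with a one-sided test (24 per arm, N = 48; power 0.801) but not with a two-sided one (30 per arm by the normal approximation, N = 60). Sidedness is a separate matter. What counts here is that the figure concerns stimulation only, and that the article gives no effect size for training against no training.

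**What can be estimated.** Write T for the effect of training, C for every other change common to both arms, and D for what tDCS adds given training.
- Mean change, active arm: T + C + D
- Mean change, sham arm: T + C
- Difference: (T + C + D) − (T + C) = D
- Mean change pooled over two equal arms: T + C + D/2

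T never appears without C, and no analysis of these two arms separates them.

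**What C contains, from the article itself.**

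| Source | Where stated | Outcomes touched |
|---|---|---|
| Recovery | Table 1 admits patients from 3 months after injury, although the Discussion calls them chronic | All |
| Retest practice | T4 repeats the T2 and T3 assessment; screening subtests are reused | Cognitive tests |
| Concurrent rehabilitation | Study setting and Discussion: patients are under a community neurorehabilitation service | All |
| Expectation | All patients know they are training | PRECiS especially |
| Regression to the mean | Entry needs WMI or VWMI below 85; the component subtests are then outcomes | WAIS/WMS subtests only |

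**Size of regression to the mean.** The index SD of 15 and the cut-off of 85 come from Recruitment. Retest reliability r = 0.8 to 0.9 and the mean μ of the referred population are assumptions. With z = (85 − μ)/15, the mean of those selected is μ − 15·φ(z)/Φ(z), and the expected retest gain with no treatment effect is (μ − selected mean)·(1 − r).

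| μ | Selected mean | Gain, r = 0.9 | Gain, r = 0.8 |
|---|---|---|---|
| 100 | 77.1 | 22.9 × 0.1 = 2.3 | 22.9 × 0.2 = 4.6 |
| 92 | 75.2 | 1.7 | 3.4 |
| 85 | 73.0 | 12.0 × 0.1 = 1.2 | 12.0 × 0.2 = 2.4 |

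This treats a single index, with the screening score as baseline. Entry is on either index and also needs FSIQ above 70, so a patient who enters on one index regresses less on the other. If the subtests are repeated before training and that repeat is the baseline, this component drops out.

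**Illustration of the risk.** Set T = 0 and D = 0, and let C be m SDs of the change score (assumed). The two-sided paired t test at .05 has noncentrality m√n; for m = 0.5 and n = 40 this is 0.5 × 6.32 = 3.16.

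| m | P(p < .05), one arm, n = 20 | P(p < .05), pooled, n = 40 |
|---|---|---|
| 0.2 | 0.14 | 0.23 |
| 0.3 | 0.25 | 0.46 |
| 0.5 | 0.56 | 0.87 |
| 0.8 | 0.92 | 1.00 |

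**The case against.** The formal objectives are already properly scoped. Aims and objectives frames transfer and 1-month maintenance, as well as the primary question, as effects of adding stimulation. Outcome measures opens with improvement in the stimulation group relative to sham, and group is a factor in the planned ANOVAs. This stands, and it means that the article largely agrees with the remedy.

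A reader might infer that the trial plans a pooled pre/post test and will report it as a training benefit. No section says so. The analysis section permits follow-up of main effects but does not say how they will be interpreted. The risk is what the wording allows, not a stated plan.

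A reader might also hold that the restorative sentence must go. It is conditional, and the Discussion places the novelty in the combination. An active-over-sham advantage on working memory would be randomised evidence that adding tDCS improves function, which partly supports the sentence. It would not show that training alone restores function, and with no compensatory arm it could not rank the two approaches.

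The regression figures do not reach the most exposed statements. PRECiS, DalCAB and the n-back were not used for selection, and regression from screening would have occurred before T3. Knowing that one was trained is common to both arms and does not by itself bias the PRECiS contrast between them.

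None of this rescues the Everyday-life definition or the claim on long-term effects of training. Both name training as the cause.

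**Conclusion.** The point holds as one of over-reach in two statements, the Everyday-life outcome definition and the Discussion's claim on long-term effects of cognitive training, and in part in the Maintenance definition. That the trial can estimate only the added effect of tDCS follows from the design and needs no assumption. The sizes are illustrative. Regression to the mean is about 1 to 5 index points, on assumed reliability and population mean, and only for WAIS/WMS scores reused from screening. For any outcome, an assumed common drift of 0.3 to 0.5 SD of the change score would be significant with probability 0.46 to 0.87 in the pooled sample with no training effect. It would be wrong to infer that the trial is invalid: the active-versus-sham comparison, primary and secondary, is untouched.

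**What to change.** - **Outcome measures, Everyday life improvement:** define the outcome as the active-versus-sham difference in change in PRECiS, which Table 5 schedules at T1, T3 and T4.
- **Outcome measures, Maintenance:** define it as the active-versus-sham difference in T3-to-T4 change, in line with Aims and objectives.
- **Analysis section:** state that change over time, within an arm or pooled, is descriptive and not attributable to training.
- **Discussion:** drop the claim about long-term effects of cognitive training. Limit the restorative sentence to the combined approach, conditional on an active-over-sham advantage, with no claim of superiority or equivalence to compensatory approaches.

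The cost is wording and a narrower stated scope; no endpoint, visit or sample size changes. Keeping the training claims would instead need an untrained or control-training arm, which cannot be sized from this article.
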